**Secondary Outcomes**

Value of care:

Value of care delivery is assessed according to the Porter value-based healthcare framework:

Patient-Value = Outcome/Costs

In the analysis, we will firstly focus on the outcome side of the value equation and assess the outcome side based on PROMs and PREMs. The categorization into suspected high-value and suspected low-value care is hence based on PROMs and PREMs. Outcomes higher than average in at least two survey periods are classified as suspected high-value care whereas outcomes lower than average in at least two survey periods are classified as suspected low-value care. Outcomes not included in one of the categories will be separated and excluded from analysis (see Figure 4).

[figure not shown]

*Figure 4: Assessment of Value-Based Healthcare - Outcome dimension*

|  | **PROM – outcome (health)** | **PREM – outcome (responsiveness)** |
| --- | --- | --- |
| **Suspected low-value care** | Maximum one standard deviations above average in at least two survey periods | Maximum one standard deviations above average in at least two survey periods |
| **Suspected high-value care** | Maximum one standard deviations below average in at least two survey periods | Maximum one standard deviations below average in at least two survey periods |
| **Measure-ment** | Separately for health-related quality of life (PROPr index score) & disease-specific health (index score of the disease-specific PROM):   - COPD-related health status - Asthma-related health status - Coronary artery disease-related health status - Diabetes-related health status (for both types) | German responsiveness questionnaire index score |

*Table 1: Assessment of Value-Based Healthcare - Outcome dimensions and measurement*

To cover the cost-side of the value equation as well, we add the health care system utilization. For each of the chronic diseases average treatment costs will be calculated. Costs will cover all healthcare related costs (see 2.6 secondary data). Depending on the deviation from the average participants are classified in the following categories:

- Low costs: More than one standard deviation below average in at least two survey periods
- High costs: More than one standard deviation above average in at least two survey periods
- Inconspicuous costs: Else

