Based on the combination of PROMs, PREMs and health care system utilization measured as costs, a value-based healthcare cube is introduced. PROM and PREM scores function as outcome dimensions and healthcare system utilization as cost dimension. Costs are hence added as new axis inside the framework (see Figure 5).

[figure not shown]

*Figure 5: Assessment of Value-Based Healthcare - Framework*

The newly introduced value-based healthcare cube allows the measurement of high-value and low-value care. Along the previously defined areas of suspected high- and low-value care (see Figure 4 and 5), the cube can be subdivided into 27 segments (see Figure 6). High-value and low-value care will be investigated based on the following criteria:

- High-value indication in both dimensions (high patient-relevant indicators (PROMs/PREMs) **at** low costs) (Figure 6 – dark green area)
- High-value indication in at least one dimension (high patient-relevant indicators (PROMs/PREMs) **or** low costs) (Figure 6 – light green area)
- Low-value indication in at least one dimension (low patient-relevant indicators (PROMs/PREMs) **or** high costs) (Figure 6 – light red area)
- Low-value indication in both dimensions (low patient-relevant indicators (PROMs/PREMs) **at** high costs) (Figure 6 – dark red area)

The value of care dimensions will be summarized into high- versus low-value care as the broad definition and into high two-sided, high one-sided, low one-sided and low two-sided value care as narrow definition. For both categorizations the frequency as well as the variation per subgroups (e.g. region, DMP etc.) will be analyzed.

[figure not shown]

*Figure 6: Assessment of Value-Based Healthcare – Framework distinguishing between high- and low-value care*

*Outcome and experience variation*

Mean change in PROM and PREM-index (sub-)scores overall and per subgroup (see 5.1 and 4.3) per disease area over time:

- Average per survey period
- Consistency over time (test-retest reliability)

Meaningful change / Minimally clinical important difference (MCID) in PROM index (sub-)scores overall and per subgroup (see 5.1 and 4.3) per disease area over time:

- Average per survey period
- Consistency over time (test-retest reliability)

*Hospital admission risk based on PROMs/PREMs and patient characteristics*

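### The low-cost cutoff, one SD below the mean of untransformed costs, cannot be met once the SD reaches the mean, which would empty the two-sided high-value category by construction

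*Protocol*

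**What the plan says.** The value-of-care part of protocol section 5.2 adds a cost axis to the PROM and PREM axes. The reference is disease-specific: "For each of the chronic diseases average treatment costs will be calculated". The scope is wide: "Costs will cover all healthcare related costs", with a pointer to the claims data in section 2.6. Three levels follow. The bottom one is defined as "Low costs: More than one standard deviation below average in at least two survey periods". The top one applies the same distance on the upper side of the mean, again with two qualifying periods required. All remaining patients form a middle level labelled inconspicuous.

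The three axes form a cube of 27 segments. Its best level, "High-value indication in both dimensions", needs good PROM/PREM results together with low costs. The narrow definition reports one-sided and two-sided high- and low-value care as four separate levels. Their frequency and their variation across subgroups are to be analysed. Section 4.2 names the shares of low- and high-value care as outcomes of the second research question.

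For this rule the protocol states no log scale, percentile or trimming. It gives no cost mean or SD, and it does not say whether the average and SD are taken per quarter or over the year.

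**The concern.** A symmetric band of one SD around the mean puts similar shares in both tails only if the variable is roughly symmetric. Healthcare costs are bounded below by zero and have a long upper tail, so the lower cutoff can fall to zero or below while the upper one stays within reach.

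If that happens, a reported 0% for two-sided high-value care could be read as a finding about care in Germany when the cutoff alone produced it. The one-sided levels would tilt too: low costs could no longer trigger one-sided high value, whereas high costs would still trigger one-sided low value.

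**Working it through.** **Inputs from the protocol.** Cutoffs at mean ± 1 SD, to be met in at least two of four quarterly periods (sections 2.1 and 5.2); 27 segments (section 5.2).

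**Assumed inputs.** CV from 0.5 to 3; lognormal or gamma costs; correlation 0.7 between quarters. None of these is in the protocol.

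**Step 1: the protocol's own figure.** 3 PROM levels × 3 PREM levels × 3 cost levels = 27, as stated. All three cost levels must be attainable for this count to hold.

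**Step 2: the low cutoff.** Mean − SD = mean × (1 − CV).

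- CV 0.5: 0.50 × mean
- CV 0.9: 0.10 × mean
- CV 1: 0
- CV 2: −1 × mean

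From CV 1 upward no non-negative cost lies below the cutoff. This holds for any distribution.

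**Step 3: effect on the cube.** Without a low-cost level, 3 × 3 × 1 = 9 segments cannot be filled and 27 − 9 = 18 remain. Two-sided high-value care requires low cost, so it is 0%. If mean and SD are taken per quarter, emptiness is certain once SD ≥ mean in at least three of the four quarters for a disease, because at most one quarter is then left in which a patient could qualify and two are needed.

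**Step 4: size over a range of CVs.** Simulated shares meeting each rule in at least two of four quarters (correlation 0.7; repeat runs agree to about 0.2 percentage points):

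| CV | Lognormal: low / high | Gamma: low / high |
|---|---|---|
| 0.5 | 11.7% / 14.9% | 15.6% / 16.6% |
| 0.9 | 0.3% / 11.9% | 6.4% / 15.1% |
| 1 | 0% / 11.2% | 0% / 14.8% |
| 2 | 0% / 6.7% | 0% / 10.5% |

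At CV 3 the lognormal high-cost share is 4.6%, and the low-cost share is still 0%.

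**Step 5: is CV ≥ 1 within reach?** As an illustration, let routine quarterly cost have mean 1 and CV 0.5. Let a fraction p of patients per quarter, independently of routine cost, have a hospital-type event that adds k. Then mean = 1 + kp and variance = 0.25 + k²p(1 − p).

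- p = 2%, k = 5: mean 1.10, variance 0.25 + 25 × 0.0196 = 0.74, CV = 0.860/1.10 = 0.78
- p = 3%, k = 7: mean 1.21, variance 0.25 + 49 × 0.0291 = 1.676, CV = 1.295/1.21 = 1.07
- p = 5%, k = 10: mean 1.50, variance 0.25 + 100 × 0.0475 = 5.00, CV = 2.236/1.50 = 1.49

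Modest event rates can therefore reach CV 1, but not every choice of p and k does.

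**The case against.** The strongest reply is that the decisive premise is not in the document. Without a cost mean or SD, nobody can show from the protocol that the low-cost level will be empty. Whether inpatient costs enter is also not fully settled: the inpatient entry in section 2.6 lists no cost field, although the separate hospital-care entry does and section 5.3 plans average costs of inpatient stays. This stands. The point is conditional on CV, and the data will decide.

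Three stronger inferences are tempting and are not supported:

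- *That the whole comparison of high- with low-value care is an artefact.* Section 5.2 first classifies suspected high and low value on PROMs and PREMs alone, and that analysis is untouched. High value through PROMs/PREMs also stays reachable once costs are added. What is lost is the two-sided high-value level and the low-cost route into one-sided high value.
- *That diseases with more skewed costs would look worse.* Above CV 1 the low-cost share stays at 0% while the high-cost share falls, from 11.2% at CV 1 to 4.6% at CV 3 under lognormal costs. On the cost axis such a disease would then look better.
- *That the level is nearly empty even somewhat below CV 1.* This depends on the distribution: at CV 0.9 it holds 0.3% under lognormal costs but 6.4% under gamma costs.

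It is also fair to say that this is a secondary, descriptive classification. Costs come from claims data and can be reclassified later, and section 5.1 promises sensitivity analyses for the section 4.2 outcomes. It names none for this cutoff, however, and a sensitivity analysis would leave the main definition as it is.

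**Conclusion.** The concern holds in conditional form. Where the SD of costs is at least the mean, the rule as written leaves the low-cost level empty and sets two-sided high-value care to 0%, while two-sided low-value care remains possible. That part is exact and needs only non-negative costs. Whether the condition is met is an assumption, plausible for quarterly costs that include hospital care. Below CV 1 the level is reachable but smaller than the high-cost level under both distributions examined, by an amount that depends on the distribution.

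The rule is a stated definition that can give a misleading result for a named outcome, so it should be fixed before the cost classification is run. The primary endpoint on representativeness and the PROM/PREM-only classification do not depend on it.

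**What to change.** In section 5.2, replace the raw mean ± 1 SD cost cutoffs with disease-specific lower and upper percentiles per quarter, for example the 16th and 84th, which correspond to ± 1 SD under normality (15.9% in each tail). Keep the two-period requirement. With a 15.87th-percentile cutoff and no ties, about 12.0% to 17.6% of patients would be low-cost in at least two of four quarters for between-quarter correlations of 0 to 0.8, and all 27 segments stay reachable.

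Two details belong in the same sentence:

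- *Ties at zero cost.* If more than 16% of patients have no cost in a quarter, the 16th percentile is itself zero and a strict inequality would empty the level again.
- *Source of the percentiles.* They are best taken from the full insured population with the disease, for whom section 4.1 says utilization data are available. Shares among participants are then not fixed by construction.

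The drafting cost is small and no new data are needed. The real cost is that disease-specific percentiles make the cost axis alone a less direct comparison between indications, which matters because section 1.2 asks for shares per indication. Cost shares should therefore be read through subgroups and joint cells.

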   1. STUDY DESIGN

The study is an observational prospective cohort study with patients of four chronic disease areas with existing DMPs (asthma, chronic obstructive pulmonary disease (COPD), diabetes (type 1 and type 2) and coronary artery disease) with two sub-cohorts (DMP and non-DMP) for each disease.

- Type of control: none / group matched BARMER insurees (matching criteria: disease area, gender, age group)
- Level and method of blinding: none
- Method of treatment assignment: stratified randomized selection of study population
- Number of subjects: 200,000 patients invited (50,000 per chronic indication and about 25,000 in each sub-cohort)
- Duration of study: one year (four quarterly survey periods)

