  1. INTERVENTION

In addition to filling out the survey questions at four points in time (intervention 1), all participants will receive PRO feedback as a potential nudge (intervention 2). The PRO feedback will be a pdf report sent via email and available in their study participant profile, which graphically (line charts) shows the patients’ individual generic and disease-specific health status in comparison to the individual peer group. In addition to the visual feedback, the results will shortly be explained on the same page. The description will cover whether patient-individual PRO scores are better or worse compared to the peer group, and for longitudinal values, whether patient-related changes improved or worsened. Additional details on the scores, sub-scores, and calculations are shared with the patients on the following pages of the report. Peer groups are classified according to their disease, gender, and age group. The peer group is created based on individuals who have replied to the previous survey and will only be displayed if the group consists of at least four individuals. This threshold is set by the German General Data Protection Regulation. The report refers to the patients’ physicians as the main contact to discuss the results or in case of questions.

- 1. SAMPLE SIZE

The sample is drawn stratified randomly from insured patients of one large German statutory health insurance with about 9 million insured persons (of about 73 million statutorily insured persons in total in Germany) according to their diagnosis and/or disease management program status. A one-to-one matching of participants of one DMP with non-participants of a DMP but with the same proven diagnosis according to the ICD-10-GM system is made. Further stratification criteria are age group, gender, and health system utilization.

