As shown in Figure 1, the first point of contact will be a letter from the insurance to insured individuals with chronic diseases, who can then sign into the digital study via a QR code or link. For each of the different disease areas, a distinct care path is opened, with a sign-in process followed by selected PROMs and PREMs. The study covers a timeframe of one year with four overarching time intervals with dedicated questions. These are split into smaller tasks to facilitate the answering process for participants. The time intervals are split into smaller tasks to facilitate the answering process for participants. A few weeks after responding to the first set of questions (A & B), patients will receive a report with their individual PROM scores compared to a peer group, the PRO feedback (C). From the second interval onwards, patients will also receive the PRO feedback in a longitudinal visualization. Lastly, following the PRO feedback participants will be surveyed regarding their health behavior (D).

Figure 2 presents the questionnaires that will be used in the study per chronic disease group. PROM surveys include generic as well as disease-specific PROMs. The participants will receive individual reports on their patient-specific and peer group outcomes (PRO feedback) and will be asked about the comprehensibility of the report. Following the report, the participants receive a set of questions regarding the report’s comprehensibility and their health-related behavior.

[figure not shown]

*Figure 2: Survey items in the PROMchronic trial*

The primary data collected in this study is hence:

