**Patient reported indicators:**

- Generic PROM index score: PROMIS PROPr is a preference-based score which combines seven PROMIS domains of health status into one score (cognitive function, depression, fatigue, pain, physical function, sleep, social roles)
- Disease-specific PROM index scores for each chronic disease

Asthma: Asthma Impairment and Risk Questionnaire (AIRQ) score

COPD: Clinical COPD Questionnaire (CCQ) score

Diabetes: Problem Areas in Diabetes (PAID-5) score

Coronary artery disease: Seattle Angina Questionnaire (SAQ-7) score and Rose Dyspnea Scale (RDS) score

- PREM index score: Responsiveness of the health care system
- Looked at PRO feedback
- Comprehensibility of PRO feedback
- Helpfulness of PRO feedback
- Emotional reaction to PRO feedback
- Discussion of PRO feedback with physician(s)
- Health behavior in five dimensions:

Physical activity

Nutrition

Tobacco consumption

Alcohol consumption

Sleep duration

- Plans to change health behavior in the future
- Trigger for health behavioral change
- Overall health improvement
- Disease-specific health improvement

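### Consistency of scores across quarterly surveys in all participants is labelled test-retest reliability, but it mixes measurement error with true change

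*Protocol*

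**What the plan says.** Protocol Section 5.2, under Outcome and experience variation, plans two sets of summaries over the survey periods. The first is "Mean change in PROM and PREM-index (sub-)scores overall and per subgroup", the second "Meaningful change / Minimally clinical important difference (MCID) in PROM index (sub-)scores overall and per subgroup". Under each, the same two bullets follow: an average per survey period, and "Consistency over time (test-retest reliability"). Section 3 puts all analyses on all participants except those who withdraw consent, and nothing limits the consistency bullet to a stable subset.

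The conditions between surveys are set out elsewhere:

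- Section 2.1: "Duration of study: one year (four quarterly survey periods"), in asthma, COPD, diabetes and coronary artery disease.
- Section 2.4: "all participants will receive PRO feedback as a potential nudge (intervention 2"). The report points patients to their physicians as the people to discuss it with.
- Section 2.6: a few weeks after the first questions, "patients will receive a report with their individual PROM scores compared to a peer group, the PRO feedback (C"). Then: "From the second interval onwards, patients will also receive the PRO feedback in a longitudinal visualization".
- Section 1.2 asks whether the feedback leads to behaviour change and more active participation in treatment, and whether scores can warn early of deterioration.

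**The concern.** Agreement between two administrations estimates reliability only if the person's true state is the same at both and nothing between them influences the answers. Neither condition can be presumed here. The protocol looks for real change in these same scores, over these same intervals, in these same people. It also sends them material that might alter their behaviour, their care or the way they answer next time.

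An analysis that follows the bullet as written would publish a figure that readers take as measurement quality. A sound instrument in a changing disease would look less reliable than it is. Two subgroups measured equally well could appear to differ in reliability merely because one changed more. For the meaningful-change item the label is harder still to interpret, because that item is itself a measure of change: in people who are truly stable, observed change is only error, so a good instrument would not show up there as consistent change.

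**Working it through.** **The plan's own figures.** The protocol gives no reliability coefficient, target or precision for this item, so there is no stated value to reproduce. Section 5.2 (Data analysis) mentions intraclass correlation coefficients, but as a general check not tied to this bullet. The one sample-size figure reproduces: 200,000 × 0.30 × 2/3 × 0.40 = 16,000 complete participants (Section 2.5). It has no bearing on whether the label is right.

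**Model.** Classical test theory: observed score = true score + error, with total variance 1 at each survey, so reliability R is the true-score variance. Let d be the SD of individual true change between two surveys, in units of the observed-score SD, and let true-score variance be equal at both surveys.

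- Var(true change) = 2R(1 − ρ) = d², so the true-score correlation is ρ = 1 − d²/(2R).
- Observed between-survey correlation = R × ρ = R − d²/2.
- If the mean also shifts by m, the two-occasion absolute-agreement ICC is (R − d²/2) / (1 + m²/2).

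R, d and m are assumptions; the protocol gives none of them.

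**Results for the correlation (m = 0).**

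| True change d | R = 0.90 | R = 0.80 |
| --- | --- | --- |
| 0 | 0.900 | 0.800 |
| 0.2 | 0.880 | 0.780 |
| 0.3 | 0.855 | 0.755 |
| 0.5 | 0.775 | 0.675 |

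For example, 0.90 − 0.5²/2 = 0.90 − 0.125 = 0.775.

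**With a mean shift.** For R = 0.90 and d = 0.3, the agreement ICC is 0.855/1.02 = 0.838 at m = 0.2 and 0.855/1.045 = 0.818 at m = 0.3. For d = 0.5 it is 0.775/1.02 = 0.760 and 0.775/1.045 = 0.742.

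**Reading.** In this model the correlation equals R only when d = 0, and the agreement ICC only when d = 0 and m = 0. Two groups with the same R = 0.90 but d = 0.2 and d = 0.5 would differ by 0.880 − 0.775 = 0.105 with no difference in measurement quality. Anchoring on previously displayed PROM scores is outside the model and would push agreement upwards, so the net direction for PROMs is not fixed.

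**The case against.** The strongest reply is that this is a loose parenthesis on a minor item, and that the coefficient, the survey pairs and any stable subset belong in a statistical analysis plan that is not shown. The second half is fair as far as it goes: those details are not missing from a protocol. But the protocol does more than stay silent. It states that consistency over the survey periods is test-retest reliability, and an analysis plan that implemented that faithfully would carry the error forward.

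Other parts of the reply stand and limit the point:

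- A reader might infer that the main research question depends on this figure. It does not. The sub-questions in Section 1.1 concern response and representativeness, and the primary endpoint compares weighted utilization with the target population. Section 4.2 places outcome variation under the second research question, with no threshold or decision attached.
- A reader might infer that pre-feedback and post-feedback periods are pooled. The protocol names no pooling rule; it merely makes no separation.
- It is tempting to say that DMP members or frequent users would look worse measured. Nothing in the protocol says they change more than their comparators.
- The report is described as showing health status and PROM scores. Nothing says PREM scores are displayed, so the anchoring argument does not extend to the PREM index.
- The feedback is a potential nudge whose effect is a study question, and Section 5.2 foresees participants who do not open the report. The point does not need the nudge to work: true change over a quarter of chronic disease is enough.
- The loss may be small. At d = 0.2 it is 0.90 − 0.88 = 0.02.

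**Conclusion.** The point holds as a mislabelled secondary analysis. All-participant consistency across quarterly surveys is not test-retest reliability in this design, and neither it nor its subgroup differences should be interpreted that way. The size cannot be derived from the protocol. Under an assumed reliability of 0.90, equal variance at both surveys and true individual change of 0.2 to 0.5 SD, the between-survey correlation falls to about 0.88 to 0.78. A mean shift would lower an agreement coefficient further, while anchoring on displayed PROM scores could raise it. The conclusion that the label is wrong does not depend on these values, only on true change being possible, which the protocol's own meaningful-change analysis presumes. The primary endpoint is unaffected.

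**What to change.** 1. In Section 5.2, call the all-participant figure *longitudinal stability*, and state that it and its subgroup differences are not read as reliability.
2. Remove the reliability label from the meaningful-change (MCID) item.
3. If a reliability estimate is wanted for PROMs, restrict it to adjacent surveys in which the participant reports no change and claims show no admission in between. Section 2.6 lists *Overall health improvement* and "Disease-specific health improvement" among the items collected. They are known here by name only, so first confirm that their response options separate no change from no improvement, which would include worsening.
4. Split that estimate descriptively by whether the participant looked at the PRO feedback, also collected. Viewing is self-selected, and stable viewers have still seen their scores, so the split does not remove anchoring.
5. Make no test-retest claim for the PREM index unless unchanged experience of care can be identified; the health items do not do that.

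Steps 1 and 2 are wording only. Step 3 uses data already planned but leaves fewer pairs per estimate. How many cannot be computed: the 16,000 expected complete participants span all four disease areas, and the share who are stable is not given.
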